## Abstract

**Background:**

Family-based interventions to prevent childhood obesity depend upon parents’ taking action to improve diet and other lifestyle behaviours in their families. Programmes that attract and retain high numbers of parents provide an enhanced opportunity to improve public health and are also likely to be more cost-effective than those that do not. We have developed a theory-informed optimisation intervention to promote parent engagement within an existing childhood obesity prevention group programme, HENRY (Health Exercise Nutrition for the Really Young). Here, we describe a proposal to evaluate the effectiveness of this optimisation intervention in regard to the engagement of parents and cost-effectiveness.

**Methods/design:**

The Optimising Family Engagement in HENRY (OFTEN) trial is a cluster randomised controlled trial being conducted across 24 local authorities (approximately 144 children’s centres) which currently deliver HENRY programmes. The primary outcome will be parental enrolment and attendance at the HENRY programme, assessed using routinely collected process data. Cost-effectiveness will be presented in terms of primary outcomes using acceptability curves and through eliciting the willingness to pay for the optimisation from HENRY commissioners. Secondary outcomes include the longitudinal impact of the optimisation, parent-reported infant intake of fruits and vegetables (as a proxy to compliance) and other parent-reported family habits and lifestyle.

**Discussion:**

This innovative trial will provide evidence on the implementation of a theory-informed optimisation intervention to promote parent engagement in HENRY, a community-based childhood obesity prevention programme. The findings will be generalisable to other interventions delivered to parents in other community-based environments. This research meets the expressed needs of commissioners, children’s centres and parents to optimise the potential impact that HENRY has on obesity prevention. A subsequent cluster randomised controlled pilot trial is planned to determine the practicality of undertaking a definitive trial to robustly evaluate the effectiveness and cost-effectiveness of the optimised intervention on childhood obesity prevention.

**Trial registration:**

ClinicalTrials.gov identifier: NCT02675699. Registered on 4 February 2016.

## Background

Although the most recent data suggest a levelling off of the prevalence of childhood obesity in the United Kingdom, levels remain high and there are clear inequalities, with rates continuing to rise in more deprived and ethnic minority groups [1]. Childhood obesity impacts physiological and psychological health, which tracks into adulthood [2, 3], increasing the risk of morbidity and mortality [4, 5]. It imposes significant costs on the U.K. economy, with an expected sevenfold increase in related NHS costs by 2020 and a forecasted £2 billion annual spend by 2030 [6]. Tackling obesity is a national public health priority in terms of both treatment and prevention. Establishing healthy behaviours in early childhood is critical for optimum growth and development [7]. Further, poor eating patterns developed early can persist and are associated with chronic diseases in adulthood (e.g., cardiovascular disease, type 2 diabetes mellitus [8]). Once established, obesity is difficult to reverse [9], strengthening the case for primary prevention [10, 11]. To reverse trends in obesity, there is a clear need to engage parents in shaping healthy weight-related behaviours in their children.

Design, implementation and evaluation of interventions to prevent or treat obesity may be expensive and time-consuming, and researchers often report a lack of effectiveness [12–15]. Within the literature on childhood obesity, low parent enrolment and attendance at group-delivered programmes, along with a lack of reported behaviour change, are commonly described to have had a substantial impact on group dynamics, effectiveness and cost-effectiveness [16–18].

There is a need for pragmatic, ‘real-world’ evaluations of interventions to understand the generalisability of the interventions across everyday practice [19, 20]. Further, in order for interventions to be accurately implemented and interpreted, the underpinning behaviour change techniques need to be clearly defined [21]. Implementation optimisation strategies can then be adopted to target a specific intervention component [22]. It is imperative that parent engagement be improved across all parenting interventions delivered in community settings to optimise their impact and so that the degree to which they are effective can be assessed with confidence. In contrast to conventional pathways, in which implementation research is conducted following trials for clinical effectiveness [23], it is argued that there is a need for comprehensive early-phase (evidentiary) evaluation and enhancement of complex interventions such as those designed to prevent childhood obesity [24], prior to the conduct of large randomised controlled trials (RCTs). This novel approach ensures that factors which limit trial outcomes, such as low adherence, are minimised prior to dedicating the resources required to conduct a large trial which may identify no evidence of effectiveness, perhaps as a result of poor compliance.

The present trial involves the evaluation of an implementation enhancement ‘optimisation intervention’ of an existing preschool obesity prevention group programme, HENRY (Health Exercise Nutrition for the Really Young), to promote parent enrolment and attendance prior to establishing its clinical effectiveness and cost-effectiveness. HENRY is an 8-week group-delivered programme provided to parents of preschool children. It was developed in 2006 with joint funds from the Department of Health and the Department for Education (then called the *Department of Children, Schools and Families*) and is currently commissioned and delivered across the United Kingdom by 32 local authorities providing more than 150 programmes each year. It is delivered in community settings, often in children’s centres by children’s centre staff [25]. HENRY uses a responsive approach to provide practical guidance and improve parenting skills aimed at enhancing family lifestyle and children’s centre environments. Preliminary data indicate that HENRY may be effective at preventing childhood obesity and improving family health [25], although there is not yet evidence from an RCT.

Despite some indications of success of HENRY from audit [25] and qualitative data [26–28], process evaluation indicates implementation targets are often not met. Lack of involvement by some parents may be a threat to the viability of this programme and other, similar community-based interventions. The effectiveness of interventions in real-world conditions may not match the efficacy found in research studies [29]. This may be particularly relevant to population-based prevention programmes, in which parents may be less likely to be motivated to attend because their children show no clinical symptoms [30, 31]. Thus, it is imperative to create tailored methods to maximise parent participation and enhance successful implementation in childhood obesity prevention programmes.

Failure to attend interventions is complicated by issues of health inequalities; socio-demographic attributes; and, in some cases, challenges related to safeguarding [30, 32, 33]. Literature on non-attendance in other areas (clinical appointments) indicates that attendance is lower in certain populations and may be an indicator of vulnerability [34]. This is pertinent to obesity because prevalence rates continue to rise in children in lower socio-economic or ethnic minority groups. In addition to the anticipated public health benefits, the economic benefits of implementation optimisation in programmes such as HENRY are substantial, with one parenting intervention calculating an extra £800 cost per child in programmes that run with 8 parents compared with those running at the intended capacity of 12 parents [35].

Unlike the development of other robust behaviour change interventions, initiatives to improve parental attendance at clinical appointments have been confined largely to simple approaches such as text reminders [34, 36, 37]. To promote behaviour change, enhance the transparency of interventions and guide their generalisability, it is recognised that a systematic approach is used during intervention development, which is underpinned by theories of behaviour change and guided by an intervention-planning framework such as the Behaviour Change Wheel [24, 38]. Lessons can be learnt from child mental health research, in which many interventions have been developed and tested using robust theory-based approaches which carefully consider parent engagement [33]. Research in this field has explored perceived barriers to participation with suggested strategies to engage parents, including promotion of self-efficacy and treatment motivation. Such strategies perceive parents as the central agents of change and aim to modify the pre-treatment experience [33, 39]. RCTs evaluating parent engagement in mental health services [40] and drug misuse [41] indicate that parental engagement can be increased with a dedicated optimisation component, although a further trial focused on cultural relevance for child behaviour problems to optimise engagement [42] did not find any increase.

To our knowledge, there are no theory-based, multi-component optimisation interventions that have been developed to optimise parent engagement in obesity prevention programmes, and which have been evaluated using an RCT design. To meet this need, we developed a parent engagement optimisation intervention following Medical Research Council (MRC) guidance for development of complex interventions [38]. The Consolidated Framework for Implementation Research was used to understand contextual factors associated with the implementation of HENRY and their impact on parent engagement [43]. The Behaviour Change Wheel [44] provided guidance for the development of the intervention, which features use of the ‘COM-B’ model (capability, opportunity and motivation) to dissect behaviours into their individual and interacting components and consider which of these should be targeted in an intervention to bring about the desired behaviour change. A rapid ethnography was conducted in five children’s centres to understand the environmental, social, psycho-social, political and economic factors associated with parent engagement in HENRY. This study gathered data from approximately 190 h of observations, 22 interviews with children’s centre managers and staff, HENRY commissioners, and HENRY coordinators and facilitators. Six focus groups were also conducted with parents who had attended the programme. We convened an intervention development team consisting of experts in intervention development, obesity, applied health and behaviour change, a local authority representative, a HENRY parent champion, a parent who has attended the programme, and a representative from the HENRY team. The intervention team used evidence from the ethnography, from the literature, and from their own experiences and expertise to develop a multi-component optimisation intervention which attempts to promote parent engagement and positive behaviour change in families by supporting local authorities, children’s centres, HENRY staff, and parents using candidate implementation and delivery strategies (Career Development Fellowship CDF-2014-07-052). Here we report the protocol of our cluster randomised controlled trial (cRCT) (using routine process data) to evaluate the optimisation intervention for its ability to engage parents in HENRY prior to conducting a further evaluation of its clinical effectiveness.

## Methods/design

### Design

This study is a two-arm, multi-centre cRCT across 24 local authorities (local governments) (supporting approximately 144 children’s centres) in the United Kingdom to determine the effectiveness and cost-effectiveness of an optimisation intervention to promote parent engagement in the HENRY programme compared with standard HENRY practice (Fig. 1). Although the children’s centres deliver the HENRY programme, owing to the multi-component and interactive nature of the optimisation intervention, local authorities will be the units of randomisation (i.e., clusters) to prevent contamination between the randomised groups. Outcomes will be assessed through routinely collected data available for each HENRY programme at the parent and children’s centre levels. Information on commissioners’ willingness to pay (within local authorities) related to the optimisation intervention will be elicited. A process evaluation will be conducted alongside the cRCT in accordance with the MRC guidance on evaluating process in complex interventions [19].

**Fig. 1 Fig1:**
[figure not shown]
Trial design flow diagram. *HENRY* Health Exercise Nutrition for the Really Young, *ITT* Intention to treat

### Objectives

Primary objectives of the trial are to determine the following:The effect of the optimisation intervention applied to HENRY compared with standard HENRY in regard to increasing parent enrolment in HENRY programmes or reducing parent attrition within HENRY programmesThe willingness to pay of commissioners of the HENRY programme per additional level of parent engagement related to the optimisation intervention (Costs will be presented as an incremental cost per increase of parent engagement, so that commissioners are able to identify the point at which additional costs are acceptably offset by the benefits of engaging effectively with parents.)

Secondary objectives of the study are to determine:The effect of the optimisation intervention on achieving combined parent enrolment, attrition and compliance targetsThe effect of the optimisation intervention on parent compliance with HENRY programme contentThe effect of the optimisation intervention on parent-reported family habits and lifestyleThe potential longitudinal impact (sustainability) of the optimisation intervention on enrolment and attrition in centres that provide data from more than one programme

### Setting

The study will be conducted in local authorities with children’s centres where staff are currently trained to deliver the HENRY programme. There are currently 32 local authorities (approximately 144 centres) in the United Kingdom running the programme, all of which provide process data to the central HENRY office for monitoring/quality assurance (QA) purposes. These data will be anonymised and transferred for analysis.

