### Sample size

We assumed that 25% of the 32 local authorities currently running HENRY will not be eligible or will opt out of the study, leaving 24 local authorities (12 per arm). Power calculations for this fixed sample size (with all eligible centres in the United Kingdom invited to take part) were therefore conducted to examine anticipated power for various intervention effects, at the 5% significance level, in each of the primary outcomes and for the composite endpoint (enrol at least eight parents per programme and retain ≥75% of parents attending five of eight sessions) (see Table 1 for scenarios). On the basis of data from previous HENRY programmes (all terms in 2014), we assumed an average of 6 children’s centres per local authority providing a total of 144 children’s centres (72 per arm), an intra-cluster correlation coefficient (ICC) between 0.05 and 0.1, a coefficient of variation in cluster size of 0.54, and the following estimates of the outcomes in the control sites (HENRY alone): 55% of centres will enrol at least eight parents per programme; 50% of centres will retain ≥75% of parents attending five of eight sessions; and 25% of centres will enrol at least eight parents per programme and retain ≥75% of parents attending five of eight sessions. Thus, with the anticipated number of centres (24 local authorities, 144 children’s centres), we will have at least 80% power to detect meaningful improvements in differences of between 25% and 30% in either of the primary endpoints or the composite endpoint at the 5% significance level, assuming the ICC is no greater than 0.05.

**Table 1 Tab1:** Power calculations for enrolment and attrition endpoints for various estimates of the intervention effect and a fixed sample size of 144 children’s centres in 24 local authorities

Outcome in the control	Percentage point increase in intervention	Power for ICC = 0.1	Power for ICC = 0.05
Enrolment (≥8 parents per programme)			
55%	5%	6%	7%
	10%	15%	18%
	15%	29%	35%
	20%	49%	58%
	25%	70%	79%
	30%	87%	93%
Attrition (≥75% of parents attending five of eight sessions)			
50%	5%	6%	7%
	10%	15%	17%
	15%	28%	34%
	20%	47%	55%
	25%	67%	76%
	30%	84%	91%
Enrolment and attrition (at least eight parents per programme and 75% of parents attending five of eight sessions)			
25%	5%	7%	8%
	10%	17%	19%
	15%	31%	37%
	20%	49%	58%
	25%	67%	76%
	30%	82%	89%

*ICC* Intra-cluster correlation coefficient

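### About 144 centres is given both as the total in all 32 local authorities and as the number left in 24; the two must be reconciled, and Table 1's power depends on which is right

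*Protocol article*

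**What the plan says.** Two counts of centres are given, with the same number for different sets of authorities.

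- Setting: "There are currently 32 local authorities (approximately 144 centres) in the United Kingdom running the programme".
- Abstract, Methods/design: "24 local authorities (approximately 144 children’s centres) which currently deliver HENRY programmes".
- Design: "24 local authorities (local governments) (supporting approximately 144 children’s centres".
- The Sample size section puts the expected loss this way: "We assumed that 25% of the 32 local authorities currently running HENRY will not be eligible or will opt out of the study". By its count 24 therefore remain, 12 in each arm. For the centres it draws on 2014 programme data and states: "we assumed an average of 6 children’s centres per local authority providing a total of 144 children’s centres (72 per arm".

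Table 1 gives power for a fixed 144 centres in 24 authorities. The accompanying text claims at least 80% power for differences somewhere between 25 and 30 points if the ICC is no more than 0.05.

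On loss of centres, Recruitment and consent lets a centre decline even where its authority takes part, and treats a centre that opts out after randomisation as withdrawn. The Exclusion criteria remove centres used in the development phase and centres that plan no programme in the trial period. The Sample size section applies its 25% loss to authorities and states no further loss of centres.

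**The concern.** Removing a quarter of the authorities should also remove some centres, yet the count is about 144 before and after. Both statements hold only if the eight lost authorities have no centres between them, and nothing in the article says so. The word approximately cannot absorb the gap, which is 36 centres on one reading (144 against 108) and 48 on the other (192 against 144).

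Table 1 is the only quantitative support for the trial's size, and the number of centres is one of its main inputs. A reader who later has to interpret a null result needs to know how many centres the trial could expect to analyse. The same applies to centres that remain in a participating authority but provide no outcome, because Table 1 counts all 144.

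**Working it through.** **Counts**

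- Setting: 144 / 32 = 4.5 centres per authority.
- Sample size: 32 × 0.75 = 24 authorities, and 24 × 6 = 144 centres.
- If 6 per authority is right: 32 × 6 = 192 centres in all.
- If 144 is the 32-authority total and the lost authorities are of average size: 24 × 4.5 = 108 centres, or 54 per arm.
- More generally, if 144 is the total and each of the eight lost authorities holds k centres on average, 144 − 8k remain. That gives 108 at k = 4.5, 120 at k = 3 and 144 only at k = 0.

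**Reproducing Table 1**

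Inputs from Sample size: 12 authorities per arm, mean cluster size m = 6, coefficient of variation 0.54, ICC 0.05 or 0.1, control rates 55% (enrolment), 50% (attrition) and 25% (composite). The two-sided 5% level is from Analysis.

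- Design effect: DE = 1 + [(1 + CV²)m − 1] × ICC. With m = 6 this is 1.3375 (ICC 0.05) and 1.675 (ICC 0.1).
- Effective n per arm: 72 / 1.3375 = 53.8 and 72 / 1.675 = 43.0.
- Power = Φ[(d − 1.96·se₀) / se₁], where d is the difference, se₀ uses the pooled proportion and se₁ the two separate proportions.
- Example, enrolment 55% against 80%, ICC 0.05: se₀ = √(2 × 0.675 × 0.325 / 53.83) = 0.0903; se₁ = √((0.2475 + 0.16) / 53.83) = 0.0870; (0.25 − 1.96 × 0.0903) / 0.0870 ≈ 0.84; power 79.9% against 79% printed.

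All 36 cells reproduce within 1.4 points, so Table 1 is correct for its inputs.

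**With 108 centres** (m = 4.5, CV kept at 0.54)

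DE = 1.241 and 1.481; effective n per arm = 43.5 and 36.5.

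| ICC | Difference | Endpoint | Table 1 | Recomputed, 144 | Recomputed, 108 |
|---|---|---|---|---|---|
| 0.05 | +25 | Enrolment | 79% | 79.9% | 70.9% |
| 0.05 | +25 | Attrition | 76% | 77.2% | 67.9% |
| 0.05 | +25 | Composite | 76% | 77.2% | 67.9% |
| 0.05 | +30 | Enrolment | 93% | 93.6% | 87.7% |
| 0.05 | +30 | Attrition | 91% | 91.5% | 84.8% |
| 0.05 | +30 | Composite | 89% | 89.9% | 82.7% |
| 0.1 | +30 | Enrolment | 87% | 87.2% | 81.2% |
| 0.1 | +30 | Attrition | 84% | 84.3% | 77.8% |
| 0.1 | +30 | Composite | 82% | 82.2% | 75.4% |

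At ICC 0.05 the loss is about 8 to 9 points at +25 and 5 to 7 at +30; the lower ends compare with the printed table, the upper ends with the recomputed 144-centre column. A noncentral t version with 22 degrees of freedom, which fits Table 1 equally well, gives 69.5/66.4/66.4% and 87.0/84.0/81.8% for 108 centres at ICC 0.05.

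**Centres that contribute no outcome**

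The article gives no rate, so this is an illustration only. Suppose 120 centres contribute (m = 5, loss spread evenly over the 24 authorities). Then DE = 1.273, effective n per arm = 60 / 1.273 = 47.1, and power at +25 points with ICC 0.05 is about 74/71/71%.

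**The case against.** The best defence is that the Setting figure is the slip. It stands alone in a parenthesis with no derivation, whereas the Sample size section builds its 144 from 24 × 6, with the 6 taken from 2014 programme data, and the Abstract and Design section agree. On that reading the planned trial total was put beside the wrong number of authorities, and Table 1 is untouched. This is plausible and the article does not rule it out. A reader might infer that planned size and power are simply overstated; the text supports that only on the other reading.

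The 108 is also a scenario. Authorities that plan to stop commissioning or run no programmes may be smaller than average, and cluster size varies considerably (CV 0.54), so the remainder could lie above 108. That stands.

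A reader might go further and use "32 local authorities providing more than 150 programmes each year" in the Background to argue that far fewer than 144 centres could run a programme in the two follow-up terms. The article does not support this. The figure is a lower bound, and the argument also needs the number of terms per year, an even spread across terms, proportional loss of authorities and the number of programmes per centre, none of which is stated.

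On centre-level loss, the mean of 6 may already count only centres that delivered programmes in 2014, and the development-phase exclusion removes at most the five centres of the ethnography. Both points are fair, but neither covers individual opt-out or a centre that runs no programme in the follow-up terms.

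Finally, the sample was fixed by availability, and even with 108 centres 80% power is reached within the 25 to 30 point range at ICC 0.05. The practical effect is therefore moderate.

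**Conclusion.** The contradiction is real: the same count cannot describe both 32 authorities and the 24 left, unless the eight lost ones have no centres. Which figure is wrong cannot be settled from the article.

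The consequence for power is conditional. If 144 is the 32-authority total and the lost authorities are of average size, Table 1 overstates power by about 5 to 9 points in the 25 to 30 point range at ICC 0.05. At ICC 0.1 and +30 points, attrition and composite fall below 80% (78% and 75%, from 84% and 82%), while enrolment stays just above. If 6 per authority is right, the Setting figure should be about 192 and Table 1 stands for its inputs.

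On either reading, Table 1 assumes that every counted centre yields an outcome, with loss allowed only at authority level. The size of that further loss is unknown. All recomputed figures keep the CV of cluster size at 0.54. Nothing here calls the design or the analysis into question.

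**What to change.** 1. Reconcile the Setting section with the Abstract, the Design section and the Sample size section: say whether about 144 is the number of centres in all 32 authorities or in the 24 expected to take part, and correct the other figure.
2. Trial status reports that randomisation is complete, so state how many authorities and centres were randomised.
3. Leave Table 1 as the record of the planning assumptions. Beside it, give power for the randomised number of centres, with its mean cluster size and CV, and for a stated range of centres that opt out or run no programme in the follow-up terms.

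The cost is a text correction and a short recalculation. No extra centres and no change to design or analysis are needed. The only downside is that the stated power may become less favourable.
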